### Sample size

To our knowledge, no previous study has determined the minimally important difference (MID) for the C-ACT for children with asthma in primary care. Therefore, we decided to extrapolate the C-ACT score of a previous study (that included 166 children aged 6–11 years with asthma from secondary care)^26^ to our sample size calculation.^23^

Considering an MID of 2, a mean C-ACT score of 19.8 and with a SD of 4.1,^26^ a sample size of 126 children will be needed to achieve a power of 80% with an alpha of 5%. Using an intracluster correlation of 0.04^31^ and inflating the sample size with 15% to take into account expected loss to follow-up, the sample size has to increase to 180 patients.

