### Primary outcome measure

The primary outcome measure is the average asthma control over 18 months measured by the C-ACT.^26 27^

The C-ACT is a seven-item questionnaire (with a recall window of 4 weeks) that addresses three questions for parents and four questions for children and has been validated in children aged 4–11 years.^27^ The C-ACT questionnaire will be filled out at baseline and at four specified times during the trial. The average C-ACT score will be determined using the measurements on baseline and 3, 6, 12 and 18 months.

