### Primary outcome measures

C-ACT scores will be analysed in a multilevel repeated measures regression model, which incorporates the C-ACT scores for all measurements, including the baseline measurement. This method takes into account within-patient correlation by modelling the covariance structures of the residuals per measurement. Several structures will be considered, starting with the unstructured covariance structure.

The differences in C-ACT scores between the two groups will be modelled by the interaction of treatment and measurement after baseline, assuming that any difference in C-ACT at baseline is due to chance. Additional variables will be considered for inclusion in the regression model if they are substantially different at baseline or if they are expected to be predictive of drop-out at a later stage.

Furthermore, a subgroup analysis will be conducted in which the total sample is divided into three groups according to their baseline characteristics; a group with insufficient asthma control (undertreated children), a group with sufficient asthma control and continuous ICS use (possible overtreated children) use and a group with the remaining children.

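### The 80% power for 2 points belongs to a single-score comparison, while the primary test is an 18-month average that the article defines in two different ways

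*Protocol article*

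**What the plan says.** **Sample size.** The article takes its figures from an earlier secondary-care study: "Considering an MID of 2, a mean C-ACT score of 19.8 and with a SD of 4.1". From these it derives 126 children for 80% power at 5% alpha. It then applies an intracluster correlation of 0.04, "inflating the sample size with 15% to take into account expected loss to follow-up, the sample size has to increase to 180 patients". Repeated measurements, within-child correlation and baseline adjustment are not mentioned.

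**Primary outcome measure.** "The primary outcome measure is the average asthma control over 18 months measured by the C-ACT". The same section then lists what goes into that average: the baseline score and the four later ones, so five in all.

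**Analyses, Primary outcome measures.** The scores go into a multilevel repeated measures model, "which incorporates the C-ACT scores for all measurements, including the baseline measurement". On the treatment effect: "The differences in C-ACT scores between the two groups will be modelled by the interaction of treatment and measurement after baseline". Any baseline difference is taken to be chance. No single averaged contrast is named.

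**The concern.** An SD of 4.1 describes one score from one child. The SD of an average of four or five correlated scores is smaller, and conditioning on baseline reduces it again. So the printed power and the 2-point detectable difference do not describe the quantity to be tested.

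The two definitions of that quantity also pull in opposite directions. Putting baseline into the average adds a score on which no treatment difference is expected, which dilutes the effect. Using baseline for adjustment sharpens the comparison. In addition, a treatment-by-measurement interaction can carry up to four terms, while the sample size is for one comparison.

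At stake is how the result is read. The power statement tells a reader how much a null result means and how small a difference the trial can detect. Here it answers for a different statistic, and it could be too low or too high depending on which section is followed.

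**Working it through.** **Inputs.** Difference 2, SD 4.1, power 80%, alpha 5% (two-sided assumed), ICC 0.04, loss 15%, N 180: Sample size. Allocation 1:1: Randomisation. Children analysed: 180 × 0.85 = 153. Assumed, because not stated: 26 equal clusters (Setting gives 13 centres and at least 14 practices, about 27) and a within-child correlation r of 0.2 to 0.8. Power uses the normal approximation.

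**1. The plan's own figure.** Total N = 4 × (1.96 + 0.84)² × 4.1² / 2² = 131.9, so 132; the article prints 126. With 63 per arm the power is 78.2%. The next step does reproduce: 126 × [1 + (m − 1) × 0.04] / 0.85 = 180 at a cluster size m of about 6.4. The gap between 126 and 132 is a separate matter. What counts here is that this is a two-group formula for a single score.

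**2. Single score, 180 enrolled.** Design effect = 1 + (153/26 − 1) × 0.04 = 1.195. SE = 2 × 4.1 × √(1.195/153) = 0.725. Power = Φ(2/0.725 − 1.96) = 79%. The difference detectable with 80% power is 2.80 × 0.725 = 2.03. This matches the printed claim.

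**3. The two versions of the primary test**, with a constant 2-point effect after baseline and equal correlation between all visits (compound symmetry). SE = 0.725 × √factor.

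- Five-score average, unadjusted: effect (0 + 4 × 2)/5 = 1.6; variance factor (1 + 4r)/5.
- Mean of four post-baseline differences, baseline-adjusted: effect 2; variance factor (1 + 3r)/4 − r².

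| r | Five-score factor | SE | Power for 1.6 | Four-visit adjusted factor | SE | Power for 2 | Detectable at 80% |
|---|---|---|---|---|---|---|---|
| 0.2 | 0.36 | 0.435 | 96% | 0.36 | 0.435 | 99.6% | 1.22 |
| 0.5 | 0.60 | 0.561 | 81% | 0.375 | 0.444 | 99.5% | 1.24 |
| 0.8 | 0.84 | 0.664 | 67% | 0.21 | 0.332 | >99.9% | 0.93 |

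The five-score average reaches 80% only if SE is at most 1.6/2.80 = 0.571, that is a factor of (0.571/0.725)² = 0.62, or r up to about 0.53. The adjusted factor peaks at 0.39 (r = 0.375), where power is 99.3% and the detectable difference 1.27.

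The table shrinks the cluster variance along with the child variance. Modelling it separately, with cluster effects persisting across visits from not at all to fully, gives 66% to 97% for the five-score average and detectable differences of 0.85 to 1.27 for the adjusted mean. If the cluster variance does not shrink at all (27 clusters), the adjusted mean still has about 97% power, with a detectable difference of at most 1.46.

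**4. Unequal correlations.** Let follow-up visits correlate f with each other and b with baseline. The factor becomes (1 + 3f)/4 − b². With b = 0.3:

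| f | Factor | SE | Power for 2 | Detectable at 80% |
|---|---|---|---|---|
| 0.7 | 0.775 − 0.09 = 0.685 | 0.600 | 92% | 1.68 |
| 0.8 | 0.850 − 0.09 = 0.760 | 0.632 | 89% | 1.77 |
| 0.9 | 0.925 − 0.09 = 0.835 | 0.662 | 86% | 1.86 |

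**5. Effect that builds up.** With differences of 0.5, 1, 1.5 and 2 at the four visits, the mean is 1.25. Under compound symmetry with r of 0.2 to 0.5 (SE 0.435 to 0.453), the adjusted mean then has power Φ(1.25/SE − 1.96) of about 79% to 82%.

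**The case against.** Sizing on a single-score SD when the within-child correlation is unknown is a common and usually cautious choice. Under the analysis section's model, a constant 2-point effect would be detected with more than 80% power in every case worked above, and nothing calls for a different number of children. That stands. So does the reply that a condensed article may leave the exact model contrast to a fuller document. It does not cover two sections that treat baseline differently, or a power figure that belongs to neither.

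Three stronger readings are tempting, and the article does not support them.

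- A reader might infer that the trial really has 99% power, or detects 1.3 points. That needs compound symmetry and a full effect from month 3. The article fixes neither: it starts from an unstructured covariance, and treatment changes after baseline could make baseline a weaker predictor.
- A reader might infer an inflated false-positive rate, about 16% to 18% if any significant visit counted as success. No section states that rule. One average is primary, and the visit-specific scores are listed as secondary outcomes.
- A reader might infer that a significant difference below 2 points will be presented as clinically important. The article does not say so. It says that, to the authors' knowledge, no minimally important difference has been determined for primary care.

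**Conclusion.** The point holds as a mismatch between the power statement and the primary test, together with an unreconciled definition of that test. Its direction depends on which section is followed. The five-score average has about 66% to 97% power and falls below 80% at the higher correlations. The baseline-adjusted mean of the post-baseline differences has about 99% or more under compound symmetry, and about 86% to 92% in the unequal-correlation examples. The detectable difference runs from about 0.9 to 1.9 points across those cases.

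All these ranges rest on assumed correlations, 153 children analysed, about 26 equal clusters and an effect constant after baseline; a slower effect lowers them. A reader might infer that the trial is underpowered or oversized. Neither follows, because the article contains no correlation from which to decide.

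**What to change.** 1. **Reconcile the outcome and analysis sections.** Name one primary contrast with one degree of freedom: the mean of the treatment differences at 3, 6, 12 and 18 months from the repeated measures model, tested two-sided at 5%. State that baseline is used for adjustment and is not part of the average. Leave the visit-specific differences as the secondary outcomes they already are.
2. **Restate the power.** Keep 180. Say that the 80% refers to a single-score comparison, and give power and detectable difference for the named contrast over a stated range of within-child correlations. Let baseline-to-follow-up and follow-up-to-follow-up correlations differ, and do not print one figure.

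The cost is wording in three sections, with no extra children, visits or data. The small downside is that the restated power depends on an assumed correlation.

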### Setting

The study will take place in academic and non-academic GP practices in the south-west region of the Netherlands. The academic network of GPs ‘PrimEUR’ in Rotterdam and the south-west of the Netherlands consists of 13 GP health centres with a total of 150 000 registered patients, including ±9000 children aged 6–12 years. This academic network aims to excel in training physicians to be GPs, to supervise medical students during their internships, to initiate healthcare innovation and to participate in research in primary care. Moreover, at least 14 (smaller) GP practices will be recruited to participate in the study. The number of participating GP practices can be enlarged by inviting more GPs to participate.

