### Randomisation

The participating health centres (ie, one or more collaborating GP practices) will be the units of randomisation. They will be randomly assigned to either the intervention or control group (‘usual care’) with a 1:1 allocation as per a computer-generated stratified randomisation schedule. When a practice nurse works for several GP practices, all these practices will be part of the same cluster and randomised as one group. When a health centre consists of several GP practices with their own practice nurse, this health centre will also be considered as one cluster. When two practice nurses are working in one GP practice (not separated), this GP practice or health centre will be randomised as one cluster. When patients are eligible for inclusion in the trial and provide informed consent, a researcher will conduct the randomisation using an online randomisation programme and the patients will be informed in which treatment arm their GP practice is randomised. The cluster randomisation is conducted within 8 weeks after inclusion of the first patient of that GP practice into the present study. All subsequent patients of the same cluster will receive the same intervention.

Stratification will be based on the size of the GP practice and the number of years of experience of the GP. For example, GP practices in a single health centre (the same postal code) will be randomised in a stratified randomisation of four groups and, therefore, evenly distributed to the intervention and the control arm to minimise differences in baseline characteristics of the patients. A block randomisation with varying blocks (ie, 2–6 blocks) will be used to equally balance both groups. The sequence is kept secret from all researchers involved in the study.

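### The printed sample-size inputs need 132 to 134 children before inflation, not 126, and the target of 180 is built on the 126

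*Protocol article*

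**What the plan says.** The Sample size section gives the inputs in one sentence: "Considering an MID of 2, a mean C-ACT score of 19.8 and with a SD of 4.1". From these it states that "a sample size of 126 children will be needed to achieve a power of 80% with an alpha of 5" per cent. It then allows for clustering and loss, "Using an intracluster correlation of 0.04" and "inflating the sample size with 15% to take into account expected loss to follow-up", and concludes that "the sample size has to increase to 180 patients".

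The Randomisation section specifies assignment "with a 1:1 allocation as per a computer-generated stratified randomisation schedule", so equal arms are the right assumption. The Sample size section does not state whether the 5% is one- or two-sided, which test was used, the mean cluster size or the design effect. The Setting section says the academic network "consists of 13 GP health centres with a total of 150 000 registered patients" and that "at least 14 (smaller) GP practices will be recruited to participate in the study", and adds that the number of practices may be increased.

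**The concern.** The difference, SD, power and alpha are all printed, so the base sample size can be checked directly, and 126 fails the check. This is not an effect of condensing a full protocol into an article, because the printed result disagrees with the printed inputs. It is also the only justification given for the trial's size, and the recruitment target of 180 in the abstract depends on it. At stake are the reproducibility of the calculation and the accuracy of the 80% power claim.

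**Working it through.** **Inputs.** From Sample size: difference 2, SD 4.1, power 80%, alpha 5%, ICC 0.04, loss 15%, final N 180. From Randomisation: 1:1 allocation. Assumed: a two-sided test.

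**Step 1: base sample size.** Formula: n per arm = 2 × (z for alpha + z for power)² × SD² / difference².

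- Two-sided, normal: 2 × (1.960 + 0.8416)² × 4.1² / 2² = 65.97, so 66 per arm and **132** in total.
- Two-sided, t-test: 66.94, so 67 per arm and **134** in total.
- One-sided 5%, normal: 51.96, so 52 per arm and 104 in total.
- Rounded z values (1.96 and 0.84): 131.8 in total, so rounding of z does not explain the gap.
- Unequal allocation raises the total above 132.

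None of these gives 126.

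**Step 2: what does give 126.** With a standardised effect of 0.5, n per arm = 2 × (1.960 + 0.8416)² / 0.5² = 62.79, so 63 per arm and 126 in total. The printed inputs give 2 / 4.1 = 0.488. An effect of 0.5 results from SD 4.0 with a difference of 2 (2 / 4.0), from a difference of 2.05 with SD 4.1 (2.05 / 4.1), or from rounding 0.488 to 0.5. The article does not say which, if any, was used.

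**Step 3: power at 126 with the printed inputs.** The standard error is 4.1 × √(2/63) = 0.7305, and 2 / 0.7305 = 2.738. Subtracting 1.960 leaves 0.778, which is 78.2% power. The t-test gives 77.5%.

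**Step 4: from 126 to 180.** The design effect is 1 + (m − 1) × 0.04, with m the mean number of children per cluster.

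- Loss applied as division by 0.85: 180 × 0.85 / 126 = 1.214, so m is about 6.4.
- Loss applied as multiplication by 1.15: 126 × 1.24 × 1.15 = 179.7, so m is about 7.

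Both readings reproduce 180 with about 6 to 7 children per cluster. As a rough cross-check, 13 centres plus 14 practices would give 180 / 27 = 6.7.

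**Step 5: the same inflation from the corrected base.**

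- Overall factor 180 / 126: 132 becomes 188.6 and 134 becomes 191.4.
- m = 7 with × 1.15: 132 becomes 188.2 and 134 becomes 191.1.

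The target would therefore be about 188 to 192.

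**Step 6: power at 180 for the stated comparison.** With 15% loss, 180 × 0.85 = 153 children are analysed. Dividing by the design effect gives the effective number.

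| Children per cluster (assumed) | Design effect | Effective N | Power, normal | Power, t-test |
|---|---|---|---|---|
| 5 | 1.16 | 131.9 | 80.0% | 79.4% |
| 6 | 1.20 | 127.5 | 78.6% | 78.0% |
| 7 | 1.24 | 123.4 | 77.3% | 76.7% |
| 8 | 1.28 | 119.5 | 76.0% | 75.3% |

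**The case against.** The strongest reply is that the discrepancy hardly matters. It is 6 to 8 children and about 2 points of power before inflation. The planned analysis is a repeated-measures model that includes baseline, which should be more precise than a two-sample comparison of single scores. A baseline correlation of about 0.21 would by itself close the gap, since 132 × (1 − 0.21²) = 126.2. This stands as an argument about consequences. It does not justify the printed 126, because the Sample size section claims no gain from baseline or repeated measures.

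The reply is also right against several stronger readings that a reader might infer:

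- **That 180 cannot deliver 80% power.** This depends on a cluster size the article does not state. At 5 or fewer children per cluster, 180 gives about 80% or more by the normal formula.
- **That an SD of 4.0 must have been used.** A difference of about 2.05, which would print as 2, or an effect size rounded to 0.5 gives the same 126.
- **That power is really 75–76%.** That figure needs 27 clusters and a t reference on 25 degrees of freedom. The Setting section gives a minimum number of extra practices and allows more, while the Randomisation section merges practices that share a nurse. The number of clusters is therefore not fixed.
- **That sizing on a single score is an error because the primary outcome is an 18-month average.** This is a common simplification, and here a conservative one. As an illustration, take the mean of four post-baseline scores with an assumed within-child correlation of 0.7, and apply the same ICC to that mean. The SD becomes 4.1 × √((1 + 3 × 0.7)/4) = 3.61, and power at an effective 126 is about 87%. A lower correlation gives more.

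**Conclusion.** The base figure of 126 is wrong for the inputs as printed; they require 132 (normal) or 134 (t-test). This assumes a two-sided test and equal arms, and a one-sided test does not rescue the figure. The base is 5–6% too small.

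Carried forward, the target consistent with the printed inputs is about 188 to 192. At the 6 to 7 children per cluster that the step to 180 implies, 180 gives roughly 77–79% power for the stated single-score comparison. That range depends on the unstated cluster size, so the documents support no categorical statement that the trial is underpowered. The defect lies in the reported calculation. It does not show that the planned analysis is short of patients.

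**What to change.** Amend the Sample size section in one of two ways:

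1. Replace 126 with 132 (normal) or 134 (t-test), and state that 180 children with 15% loss give about 77–79% power for this comparison, naming the assumed mean cluster size; or
2. State the unrounded difference, SD or standardised effect that was actually used and yields 126. An SD of 4.0 should be printed only if it was in fact the input, since the text cites 4.1 from its source.

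In either case, state that the test is two-sided, if it is, and give the mean cluster size behind the design effect.

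Optionally, keep 180 and also quote its power for the planned baseline-inclusive repeated-measures analysis, with the assumed within-child correlation and the visits that enter the contrast.

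The cost is a few lines of text. Under the first option the quoted power becomes slightly less favourable. No extra patients and no change to design or analysis are needed.

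### The sample-size chain from SD 4.1 to 126 to 180 children does not give the stated 80% power on its own inputs, mainly because 126 matches an SD of 4.0

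*Protocol article*

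**What the plan says.** All of the calculation is in the Sample size section of the protocol article.

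- Effect and spread: "Considering an MID of 2, a mean C-ACT score of 19.8 and with a SD of 4.1".
- Base: "a sample size of 126 children will be needed to achieve a power of 80" per cent, "with an alpha of 5" per cent. Whether the test is one- or two-sided is not stated.
- Clustering and loss: "Using an intracluster correlation of 0.04" and "inflating the sample size with 15% to take into account expected loss to follow-up", after which "the sample size has to increase to 180 patients".

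No mean cluster size, number of clusters, variation in cluster size or inflation formula accompanies these figures.

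Other sections bear on the clusters. Setting describes an academic network of 13 health centres and adds: "Moreover, at least 14 (smaller) GP practices will be recruited to participate in the study". It also says that the number of practices can be enlarged. Randomisation allocates clusters "with a 1:1 allocation as per a computer-generated stratified randomisation schedule". There a cluster may be a single practice, several practices that share a nurse, or a whole health centre.

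**The concern.** The 80% power and the allowance for loss to follow-up both rest on this one paragraph. Three of its steps can be tested: whether 126 follows from the stated difference and SD, whether adding 15% covers a loss of 15%, and whether the clustering allowance suits clusters that are likely to differ in size. Each of these, if wrong, errs towards overstating power. A reader who takes 80% at face value would misjudge what a null result on the primary outcome means.

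**Working it through.** **Inputs.** From Sample size: difference 2, SD 4.1, power 80%, alpha 5% (taken as two-sided), ICC 0.04, loss 15%, total 180. From Randomisation: 1:1 allocation. From Setting: 13 centres plus at least 14 practices, so about 27 sites. Assumed, because not stated: mean cluster size m and its CV.

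**Step 1: the base.** Total N = 2 × [2 × SD² × (1.960 + 0.842)² / 2²], each arm rounded up.

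- SD 4.1: 65.97 per arm, so 66 and N = 132. A t-test needs 67 per arm, N = 134.
- SD 4.0: 62.79 per arm, so 63 and N = 126, the plan's figure.
- SD 4.1, one-sided 5%: 104, so sidedness does not explain 126.

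Power of 126 children at SD 4.1: the standard error is 2 × 4.1/√126 = 0.7305, 2/0.7305 = 2.738, and Φ(2.738 − 1.960) = 78.2%, before clustering or loss.

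**Step 2: from 126 to 180.** The design effect with equal clusters is 1 + (m − 1) × 0.04.

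| m | Design effect | 126 × design effect | × 1.15 | ÷ 0.85 |
|---|---|---|---|---|
| 6 | 1.20 | 151.2 | 173.9 | 177.9 |
| 6.36 | 1.2144 | 153.0 | 176.0 | 180.0 |
| 6.67 (180/27) | 1.2268 | 154.6 | 177.8 | 181.9 |
| 7 | 1.24 | 156.2 | 179.7 | 183.8 |

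So 180 is reproduced by × 1.15 at m = 7, and also by ÷ 0.85 at m = 6.36. The wording favours × 1.15, but the figure alone cannot settle which was used. At m = 7 the two rules differ by 183.8 − 179.7, about 4 children. Taking 126 as given (SD 4.0), 153 evaluable children at m = 7 give 79.3%, under one point short.

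**Step 3: power after the stated loss.** 180 × 0.85 = 153 evaluable. The design effect is 1 + [(1 + CV²)m − 1] × 0.04, the effective N is 153 divided by it, and power = Φ(2/(2 × SD/√effective N) − 1.960). In this step m is the mean number of evaluable children per cluster; 153/27 = 5.67.

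Power at SD 4.1, normal reference:

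| m | CV 0 | CV 0.4 | CV 0.8 |
|---|---|---|---|
| 5.67 | 79.1% | 77.9% | 74.4% |
| 6 | 78.6% | 77.4% | 73.7% |
| 7 | 77.3% | 75.9% | 71.7% |

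Worked case, m = 5.67 and CV 0: design effect 1.187, effective N 128.9, standard error 0.722, ratio 2.769, Φ(0.809) = 79.1%.

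With 27 clusters and a t reference on 25 df, the first row becomes 75.9%, 74.6% and 71.0%, roughly 3 points lower.

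The CV range is illustrative. If the 13 centres gave 9 to 12 children each and 14 practices shared the rest of 180, the CV would be 0.34 to 0.77. Those counts are not in the article.

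**Step 4: separating the causes.** With the base of 126 taken as given (SD 4.0), 153 children in 27 equal clusters give 81.0%. At SD 4.1 the same case gives 79.1%. At equal cluster sizes, then, the SD mismatch accounts for the fall below 80% in this case.

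**The case against.** A reader might infer that the 15% multiplier and an equal-cluster assumption are what break the calculation, and that 180 children tolerate only a 13.2% loss (1 − 156.2/180). The article does not support that. It states neither the cluster size nor the formula, and it never says that clusters were taken as equal. A mean cluster size need not be a whole number, so ÷ 0.85 at 6.36 cannot be excluded. The 13.2% figure also holds clusters at 7 while children leave, although loss shrinks clusters. With 27 clusters and the base of 126, the evaluable number needed solves n = 126 × [1 + (n/27 − 1) × 0.04], so n = 148.7 and the tolerated loss is about 17.4%. This objection stands in full: the loss step is a minor contributor.

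The unequal-cluster figures rest on an assumed CV. The article does not say that all 13 centres enrol or how many children each contributes. Practices sharing a nurse are merged, and more practices may be added, so 27 sites are not necessarily 27 clusters. With smaller clusters the shortfall closes: at SD 4.1, 153 evaluable children reach 80% if equal clusters average about 5.0 (design effect 1.159, about 31 clusters). This stands as a limit on the size of the shortfall. It does not repair the derivation of 126.

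The primary analysis is a multilevel repeated-measures model that includes baseline C-ACT, and the Missing data section keeps children with incomplete follow-up. Both could raise power above the simple calculation. That also stands, but the Sample size section takes no credit for it, so its stated 80% has to be judged on the simple calculation.

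Finally, a journal article may leave cluster counts to the full protocol. Their absence is therefore not the point here; the point is that the printed inputs do not produce the printed 126.

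**Conclusion.** The stated 80% does not follow from the stated inputs. The main and firmest reason is the base: SD 4.1 needs 132 children (134 by t-test), and 126 gives 78.2% before clustering. This assumes only a two-sided 5% comparison of two means.

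After the stated loss, power is about 77–79% with equal clusters of 5.7 to 7 children. It falls to about 76–78% at CV 0.4 and 72–74% at CV 0.8, and a t reference on about 25 df takes off roughly 3 more points. These figures depend on the assumed cluster size and CV. The loss multiplier adds less than one point.

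A reader might go further and conclude that the trial is underpowered for its primary analysis or must recruit more children. The document does not show that, because the gain from baseline and repeated C-ACT scores is not quantified. The defect is a misstated power figure of modest size.

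**What to change.** Restate the Sample size paragraph:

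1. Derive the base from SD 4.1 (132, or 134 by t-test), or correct the SD if 4.0 was the value used. State that the test is two-sided.
2. Give the assumed mean cluster size, number of clusters and CV, and use the design effect 1 + [(1 + CV²)m − 1] × 0.04.
3. Divide by (1 − 0.15) for loss.
4. Quote the power that 180 enrolled children give under these assumptions.
5. If the repeated-measures model with baseline C-ACT is relied on to recover 80%, show that factor and the correlation it assumes.

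The cost is one rewritten paragraph and a slightly less favourable stated power. Recruitment, design and analysis stay as they are, and no additional children are needed.
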